## Abstract

**Introduction:**

Intracranial atherosclerotic disease (ICAD) is one of the most important etiologies of ischemic stroke, especially in Asia. Although medical treatment was recommended as the first-line therapy for ICAD, the recurrent stroke rate was still high in severe stenosis of ICAD despite aggressive medical treatment. Traditionally, the degree of luminal stenosis is used as the principal index for stroke risk stratification in patients with ICAD, while recent evidence suggested that symptomatic atherosclerotic plaques were characterized by plaque features and hemodynamics. This prospective, longitudinal, and nested case-control study aims to identify multimodal imaging predictors of high-risk patients with ICAD refractory to medical treatment and explore a refined risk stratification model based on the above multimodal imaging predictors.

**Methods:**

This prospective, longitudinal, and nested case-control study includes 400 symptomatic patients with ICAD with 50–99% of stenosis treated with aggressive medical therapy. All patients who meet the eligibility criteria are assessed by multimodal imaging examination from three aspects, including lumen stenosis, plaque characteristics, and hemodynamic features. The enrolled patients receive aggressive medical management, including antiplatelet therapy and cardiovascular risk control. The primary outcome is ischemic stroke or death attributable to the lesion of the target vessel within 1 year. The secondary endpoints are (1) any stroke or death; (2) all-cause mortality; (3) any stroke out of the territory of the responsible lesion; (4) functional outcome with the modified Rankin Scale (mRS).

**Ethics and Dissemination:**

This study has been approved by the ethics committee of our center ([2021]083) and has been prospectively registered (Registration No: ChiCTR2100048832). Study findings will be disseminated through peer-reviewed publications and presentations at scientific meetings.

## Introduction

Intracranial atherosclerotic disease (ICAD) is one of the most important etiologies of ischemic stroke, especially in Asia. Approximately 33–50% of cases of stroke and more than 50% of transient ischemic attacks (TIA) are attributed to ICAD, which is the most common cause of stroke burden in China (1–4). Contrary to Caucasian patients, patients in Asia with ICAD have a high occurrence rate of severe stenosis and multiple risk factors, such as hyperlipidemia, diabetes mellitus, a family history of stroke, smoking, heavy drinking, and overweight (5–7).

The primary treatments for ICAD are medical treatments and endovascular treatments. Endovascular treatments, such as primary angioplasty, balloon-mounted stent, and self-expansion stent, were regarded as a substitution for patients refractory to medical treatment (8). According to previous randomized control trials studies, endovascular treatment for symptomatic ICAD was related to a higher recurrent risk of stroke (19.7–36.2%) than medical treatment (9, 10), while it may provide benefits over medical treatment with tailored patient selection and operator credentialing (11, 12). Medical treatment, comprising antithrombotic therapy, lipid-lowering treatment, and risk factor modification, was recommended as the first-line therapy for ICAD since the Stenting vs. Aggressive Medical Therapy for Intracranial Arterial Stenosis (SAMMPRIS) trial suggested that medical treatment was superior to the endovascular treatment. However, the recurrent stroke rate ranged from 12.2 to 23% per year in patients with severe stenosis of ICAD even under aggressive medical treatment (8–10, 13, 14).

A great deal of effort has been invested in early identification of high-risk patients with ICAD despite aggressive medical treatment for alternative therapy, such as endovascular therapy, but with limited effect. Traditionally, the degree of luminal stenosis referred to the Warfarin-Aspirin Symptomatic Intracranial Disease (WASID) criteria is used as the principal and is somehow the only index for stroke risk stratification in patients with ICAD, which is simple but may not be sufficiently distinguishable (15). Recent evidence suggested that symptomatic atherosclerotic plaques were characterized not only by a severe degree of luminal stenosis but also by the features such as plaque instability and hemodynamic compromise (16).

Plaque features including specific plaque components, such as large lipid core, thin fiber cap, incomplete fiber cap, intra-plaque hemorrhage, and inflammatory cell infiltration around the lesions, have been collectively characterized as “plaque instability,” which has been demonstrated to be associated with risk of distal embolization or cerebral blood flow deficits (17–19). High-resolution MRI (HR-MRI), which is an emerging effective non-invasive technique, has been used to assess the above features in practice. For instance, intra-plaque hemorrhage and plaque enhancement were detected on HR-MRI in more than 1/2 and 2/3 of patients with ischemic stroke caused by ICAD, respectively (20–22). Hemodynamic compromise, namely hypoperfusion, is another important dimension of ICAD assessment and would impair the washout of debris during distal intracranial circulation, leading to artery-to-artery embolism infarction and increasing the risk of ischemic events (23). Studies have reported that the hazard ratio of ischemic stroke in ICAD patients with hemodynamic compromise was higher with a range of 2–3.5 compared with ICAD patients without hemodynamic compromise after adjusting age and other cardiovascular risk factors (24–27). Cerebral hypoperfusion could be evaluated by several imaging techniques, including CT perfusion, perfusion-weighted imaging, and arterial spin labeling (ASL). In contrast to CT perfusion and perfusion-weighted imaging, ASL is a non-invasive magnetic resonance perfusion imaging method used to visualize and quantify cerebral bleed flow without exogenous contrast agents. Computational fluid dynamics (CFD) simulation is an effective supplement to ASL for hemodynamic evaluation, which could be applied for the interpretation of local flow properties such as translesional pressure drop, wall shear stress, and filtration rate of low-density lipoprotein (28–30). In this study, we have described the methods and procedures used in this prospective, longitudinal, and nested case-control study.

## Methods and Analysis

### Study Design

This is a prospective, longitudinal, and nested case-control study of patients with ICAD who are treated with aggressive medical therapy in a tertiary hospital in northern China (Trial Registration No: ChiCTR2100048832) (Figure 1). This study aims to (i) identify multimodal imaging predictors of refractory to medical treatment of high-risk patients with ICAD and (ii) explore and validate a refined risk stratification model for patients with ICAD based on the above multimodal imaging predictors.

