### Statistical Analysis

The results will be analyzed with the intention-to-treat method. All confounding factors that influenced outcomes will be analyzed, such as demographic data, cerebrovascular events, lesion characteristics, and laboratory examination results. Student *t*-test will be used for continuous variables, while the Mann-Whitney test will be used for ordinal variables. Count data of categorical variables will be analyzed by the Chi-square test or Fisher's exact probability method. *P* < 0.05 is considered statistically significant.

Subsequent multivariate analysis by logistic regression will be performed to detect independent relevant factors influencing primary endpoints. The regression coefficient of independent variables is defined as the weight of this variable for an evaluation system. If there are difficulties for building an evaluating system by the logistic regression model, we will attempt to establish the decision tree with high sensitivity for the evaluation system by Random Forest regression (34).

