## Discussion

Intracranial atherosclerotic disease is the primary cause of stroke, especially in Asia, which caused high burdens of mortality and morbidity despite the latest treatment strategies, including medical management, endovascular treatment, and surgery (5). The effect of medical management seems ideal for a majority of patients with ICAD, while the current evaluation system cannot accurately predict those with a high risk of recurrent stroke under aggressive medical management (35). Although recurrent stroke is the multifocal cause in patients with symptomatic ICAD, studies have shown that the culprit lesion of ICAD was the major cause (36). Therefore, treatment for ICAD should be mainly focused on the culprit lesion. For the patients' refractory to medical management, other therapy strategies, such as endovascular treatment or surgery with direct intervention, has been adopted according to the current guideline recommendation (8, 13).

However, early diagnosis of high-risk patients' refractory to medical treatment and early triage to alternative therapy is limited by the current risk stratification system, which is merely based on the degree of luminal stenosis (37). The inclusion of the plaque characteristics and hemodynamics assessment with multimodal imaging method may provide a potential solution to make accurate risk stratification (22). To the best of our knowledge, the current study will be the first research to involve multimodal imaging evaluation from three aspects, including the degree of luminal stenosis, plaque characteristics, and hemodynamics, and plan to establish the prognosis prediction system for patients with ICAD who have medical treatment.

As an observational study, several potential limitations must be considered. The collected data may not be as robust as randomized control studies with blinding performance, while the randomized control studies may be needed to further confirm the results of the present study. Data collection and analysis will perform repeated verification and blinding assessment, respectively. Moreover, the study population will be focused on Chinese patients with ICAD; hence, caution must be applied when implementing the findings of this study in other ethnicities.

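### Aim (ii) is a risk model refined relative to luminal stenosis, but the stated analysis never compares the new model with stenosis alone or says that stenosis stays in it

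*Protocol article*

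**What the plan says.** The second aim, under Study Design, is to "explore and validate a refined risk stratification model for patients with ICAD based on the above multimodal imaging predictors".

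The article says what is to be refined. In the Introduction, degree of luminal stenosis "is used as the principal and is somehow the only index for stroke risk stratification in patients with ICAD". In the Discussion, early triage is "limited by the current risk stratification system, which is merely based on the degree of luminal stenosis", and the proposed improvement is this: "The inclusion of the plaque characteristics and hemodynamics assessment with multimodal imaging method may provide a potential solution to make accurate risk stratification".

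The Statistical Analysis section lists these steps:
- Univariable tests of factors "such as demographic data, cerebrovascular events, lesion characteristics, and laboratory examination results", with significance at P < 0.05.
- A multivariable step: "Subsequent multivariate analysis by logistic regression will be performed to detect independent relevant factors influencing primary endpoints".
- Score construction: "The regression coefficient of independent variables is defined as the weight of this variable for an evaluation system".
- If that proves difficult, a fallback: "we will attempt to establish the decision tree with high sensitivity for the evaluation system by Random Forest regression".

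No stenosis-only model appears in this sequence. Nor does a test of what imaging adds to stenosis, or any measure of discrimination or calibration relative to stenosis.

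**The concern.** The aim is comparative and the stated analysis is not. A multivariable model can show that a marker is associated with the endpoint, and its coefficients can be made into a score. Neither result says how well stenosis alone would have ranked the same patients. The only performance property mentioned, sensitivity in the fallback, is not expressed relative to stenosis, and a rule that labels most patients high risk can meet it.

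Stenosis is at best covered by the general category of lesion characteristics. Nothing says it is kept in the model whatever its P value, so the benchmark's place in the final score is open.

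The Discussion presents the work as a route to earlier triage of patients whose disease is refractory to medical treatment. A reader of the results would need to know whether plaque and hemodynamic imaging improve on the current index, and by how much. Followed as written, the analysis does not produce that quantity.

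**Working it through.** **Inputs from the article**
- About 400 recruited, 10% loss to follow-up, 1-year event rate 8.98%, hazard ratio (HR) 2.4 for normal versus compromised hemodynamics (Sample Size).
- Imaging measures beyond lesion geometry (Baseline Evaluations and Data Collection): 3 plaque measures (remodeling index, plaque burden, signal intensity), 2 from ASL (hypoperfusion, arterial transit artifact) and 3 from CFD (pressure drop, wall shear stress, LDL filtration rate). Total 8.

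**Assumptions not in the article**
- Stenosis log odds ratio 0.4 per SD, so OR = exp(0.4) ≈ 1.49.
- The 8 imaging measures are independent of each other and of stenosis, and have no effect.
- For power: half of patients exposed, two-sided 5%, unless stated otherwise.

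**1. The plan's own figure.** Schoenfeld events = (z_α + z_β)² / [0.25 × (ln 2.4)²], with 0.25 × 0.8755² = 0.1916.
- One-sided 5%, 80% power: (1.645 + 0.842)² / 0.1916 → 33 events; 33 / 0.0898 → 368; 368 / 0.9 → 409. This is close to 400.
- Two-sided 5%, 80% power: 41 events → 457 → 508. This does not match.
- Two-sided 80% power gives 412 if 8.98% is the rate in unexposed patients and one third are exposed.

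The match is not unique, because power, sidedness and exposure share are not given. In every version the size rests on one hazard ratio, not on a gain over stenosis.

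**2. Information available.** Evaluable patients: 400 × 0.9 = 360. Expected events: 360 × 0.0898 = 32.3. Stenosis plus 8 measures is 9 coefficients, so 32.3 / 9 = 3.6 events per coefficient.

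**3. What the stated analysis shows if imaging adds nothing.** Simulation of 1,000 cohorts of 360 patients (about 31 events each):

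| Result | Stenosis alone | Stenosis + 8 null measures |
|---|---|---|
| Mean AUC, own data | 0.613 | 0.688 |
| Mean AUC, new data | 0.606 | 0.564 |

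- The larger model has the higher apparent AUC in 99.8% of cohorts. The mean apparent gain is 0.688 − 0.613 = 0.075.
- In new data the change is 0.564 − 0.606 = −0.042.
- At least one imaging measure reaches P < 0.05 in 34.6% of cohorts. The closed form agrees: 1 − 0.95⁸ = 33.7%. With 5 to 12 null measures it is 23% to 46%.
- A nested likelihood-ratio test of the 8 measures given stenosis is positive in 6.2%, close to its nominal 5%.

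**4. What a comparison can detect if hemodynamics has the assumed effect.** Noncentrality = 32.3 × 0.1916 ≈ 6.19.
- Hemodynamic marker alone, 1 df: power about 70%.
- One block test containing that marker and otherwise null measures: about 37% at 8 df and 33% at 10 df. A logistic simulation gave 33% and 31%.

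A single block test of every imaging measure would therefore usually miss the effect on which the study was sized.

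**The case against.** **The article is condensed.** The full protocol and any SAP are not shown, and performance measures or a validation method may be set out there. This stands as a limit: the text does not support saying that no comparison exists anywhere, or that validation is absent, since the aim itself includes validating the model. But the section is not silent on model building. It goes from screening through score weights to a fallback, and the comparison it leaves out is the substance of aim (ii).

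**Refinement is an aim, not a claim.** This is correct. A reader might infer that the study will call its score better whatever the data show. No sentence says so, and the Discussion is tentative. The point is only that the stated steps would not supply the evidence.

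**Multivariable adjustment already handles stenosis.** This is partly right. Lumen stenosis is one of the three assessed aspects, and if it is entered, imaging coefficients are adjusted for it. But adjusted association is not better stratification, and in the simulation about a third of studies showed a spurious independent marker with stenosis in the model.

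**Stenosis would be dropped if it missed P < 0.05.** A reader might infer this from the order of the steps. The article gives P < 0.05 as a general significance level and states no entry or retention rule, so this is a possibility and not a planned step.

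**The simulation mainly shows overfitting.** This is largely true: a nested model with more terms almost always has the higher apparent AUC. That is why a comparison with stenosis is informative only if corrected for optimism. The null scenario also departs from the plan's own HR of 2.4. It shows what the stated analysis cannot rule out, not what is expected.

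**Conclusion.** The concern holds as a mismatch between the stated aim and the stated analysis. Aim (ii) is relative to luminal stenosis. The Statistical Analysis section contains no comparison with stenosis alone and does not say that stenosis is retained, so its outputs would not by themselves show better stratification.

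If 8 imaging measures added nothing, the larger model would look better on its own data in nearly every study, lose about 0.04 in AUC in new patients, and show at least one spurious independent marker in about a third. The event count follows from the article. The AUC figures rest on the assumed stenosis effect (OR about 1.5 per SD) and on independent null measures, and the one-third figure moves between 23% and 46% with 5 to 12 measures.

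This should be corrected before analysis. It does not invalidate the data collection or the first aim of identifying predictors.

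**What to change.** Add to the Statistical Analysis section:
1. A base model with degree of stenosis as a continuous term, always retained.
2. An extended model adding a small prespecified set of plaque and hemodynamic measures. The binary hemodynamic marker used in the sample size is tested first, on 1 df, given stenosis.
3. The bootstrap optimism-corrected difference in c-statistic between the two models, with its 95% interval, and calibration. Every selection step is repeated inside the bootstrap.
4. The same comparison for any random-forest fallback.
5. A statement that the model will be described as improving on stenosis only if this comparison supports it, and otherwise that no improvement was shown.

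The conclusion should not rest on one block test of all imaging measures, given its power of about 33% to 37%.

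Cost: modest extra analysis on data already planned, with no change to the sample size. The marker list must be kept short, and with about 32 events the study may have to report no demonstrated gain. Even the 1-df test has only about 70% power under the assumptions above.

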**Figure 1 F1:**
[figure not shown]
Schematic representation of the study.

### Patient Selection

Patients diagnosed with symptomatic ICAD (≥ 50% stenosis) in the anterior circulation in our center will be enrolled in this study from December 2021 to November 2024. Participants will be required to sign informed consent prior to data collection and documentation. All patients will receive the cerebral artery imaging examination. Patients with more than 50% of stenosis in the extracranial carotid on the ipsilateral side will be excluded through transcranial Doppler ultrasound. Detailed inclusion and exclusion criteria are described in Table 1.

**Table 1 T1:** Inclusion and exclusion criteria for patient selection.

**Inclusion criteria**	**Exclusion criteria**
1. Patients with symptomatic ICAS with culprit artery in the anterior circulation. 2. Patients aged from 18 to 80 years. 3. Stenosis of 50% to 99% (measured with WASID method) on TCD, CTA, or MRA initially, confirmed on DSA. 4. Informed consent is available from the patient or legal guardian.	1. Non-atherosclerotic lesion, for instance, moyamoya disease, vasculitis, vascular dissection, autoimmunity diseases, and developmental or genetic abnormalities. 2. More than 50% of stenosis in extracranial carotid on ipsilateral side. 3. Large cerebral infarction ( ≤ 1/2) identified by DWI and the baselin modified Rankin score of ≥3. 4. Antiplatelet drugs or statins are contraindicated. 5. MRI cannot be completed due to metal implants or claustrophobia.

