#### Endpoint Evaluation

The primary endpoint of this study is be the ischemic stroke or death attributable to the lesion of the target vessel within 1 year after enrollment. The secondary endpoints are (1) any stroke or death; (2) all-cause mortality; (3) any stroke or death out of the territory of the responsible lesion, including hemorrhagic stroke, non-local ischemic stroke, and non-responsible vascular death; (4) functional outcome with the modified Rankin Scale (mRS).

Ischemic stroke is defined as the sudden onset of a new focal neurological deficit, such as hemiplegia, hemianopia, aphasia, dysphagia, sensory disorders, or confusion, lasting over 24 h, with new cerebral infarctions detected by MRI or CT. The classification of ischemic stroke for the responsible lesion is referred to as infarction location, as infarction in or out of the territory of the symptomatic intracranial artery. Hemorrhagic stroke is defined as the sudden onset of neurological deficits, with parenchymal, subarachnoid, or intraventricular hemorrhage detected by CT or MRI (33).

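### Exclusion criterion 3 contradicts itself on infarct size and leaves unclear whether infarct and mRS exclude jointly or separately

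*Protocol article*

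**What the plan says.** The Patient Selection section hands eligibility to a table: "Detailed inclusion and exclusion criteria are described in Table 1". In that table the third exclusion reads "Large cerebral infarction ( ≤ 1/2) identified by DWI and the baselin modified Rankin score of ≥3".

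The line has two limbs. The first is infarct size on DWI, given as a label (large) with a bracketed bound (at most 1/2). The second is a baseline mRS of 3 or more. They are linked by 'and'.

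The next exclusion, "Antiplatelet drugs or statins are contraindicated", uses 'or' where either condition is evidently enough. No other section of the article gives an infarct-size limit or a baseline mRS limit.

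**The concern.** An exclusion headed 'large' should have a lower bound, with infarcts beyond some size leaving the study. The printed bound is an upper one. Someone screening from the symbol and someone screening from the word would sort the same patient differently.

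The connector adds a second uncertainty. If both limbs must hold, a patient who meets only one stays in. If the line is a list of two exclusions, that patient goes out.

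What is at stake is who is in the cohort, and therefore to whom the resulting risk model applies. Infarct burden and baseline disability also plausibly bear on outcome assessment. The stroke definition requires a new deficit "lasting over 24 h, with new cerebral infarctions detected by MRI or CT", and mRS is itself a secondary endpoint. That link is inference; the article does not state or quantify it.

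**Working it through.** The article gives no figure to reproduce here, so the check is a truth table.

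**Inputs**, all from Table 1, exclusion criterion 3:
- Infarct limb: "Large cerebral infarction ( ≤ 1/2) identified by DWI"
- Disability limb and connector: "identified by DWI and the baselin modified Rankin score of ≥3"

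**Step 1. Readings.** The sign can be taken as printed (≤ 1/2) or reversed to agree with the label (shown as > 1/2 for illustration only). The connector can be joint (both limbs needed) or separate (either limb is enough). That gives four readings:
- A: sign as printed, joint (the literal text)
- B: sign as printed, separate
- C: sign reversed, joint
- D: sign reversed, separate

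**Step 2. Patient groups.** Patients with an infarct on DWI fall into four groups, by size (≤ 1/2 or > 1/2) and baseline mRS (0–2 or ≥ 3).

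**Step 3. Status under this criterion alone.**

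| Infarct | mRS | A | B | C | D |
|---|---|---|---|---|---|
| ≤ 1/2 | 0–2 | kept | excluded | kept | kept |
| ≤ 1/2 | ≥ 3 | excluded | excluded | kept | excluded |
| > 1/2 | 0–2 | kept | kept | kept | excluded |
| > 1/2 | ≥ 3 | kept | excluded | excluded | excluded |

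**Step 4. What follows.**
- Under A, one group of four is excluded: the smaller infarct with mRS ≥ 3. Both groups above 1/2 are kept. A disabled patient with a smaller infarct is turned away, while an equally disabled patient with a larger one is enrolled.
- Reversing the sign but keeping the joint reading (A to C) changes the status of both mRS ≥ 3 groups.
- With the sign reversed, moving from joint to separate (C to D) changes two groups: ≤ 1/2 with mRS ≥ 3, and > 1/2 with mRS 0–2.
- No group has the same status under all four readings.

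**Step 5. Could the sign be a text-conversion artefact?** The other inequalities nearby, ≥ 3 in the same line and ≥ 50% for stenosis in the same section, read sensibly. Conversion error is therefore unlikely, but it cannot be ruled out from the text alone. The ambiguity of 'and' does not depend on the sign.

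**The case against.** The best reply is that the word 'large' already tells the reader which patients are meant, and the symbol is one mistyped character in a visibly ill-proofed line. Nothing shows that the single centre screened by the inverted sign. This is fair: actual misapplication is not shown. It does not remove the contradiction, which sits in the only statement of the rule and which no other section corrects.

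A second reply is that 'and' need not be an error. Excluding patients who have both a large infarct and disability is coherent, and 'and' is also ordinary usage in a list. This stands. The connector is an ambiguity, not a proven mistake, and the neighbouring 'or' is only weak evidence about what was intended.

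Third, an article may leave the denominator of the fraction to the full protocol. This also stands. The missing denominator is not a separate fault, although it should be supplied when the line is corrected.

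Fourth, the primary endpoint is target-lesion stroke or death, not mRS. According to Table 3, DWI and mRS are recorded at screening, and DWI is repeated when an event occurs, so baseline comparators exist. The claim that new events would be missed is therefore unproven.

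A reader might also infer that the rule removes small-infarct patients as a class while admitting disabled patients as a class. The text does not support this. Under the literal joint reading, patients with smaller infarcts and mRS 0–2 stay eligible, and disabled patients with smaller infarcts are excluded. Under the separate reading with the printed sign, smaller infarcts do go out as a class, but so does everyone with mRS ≥ 3. No single reading gives both halves.

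**Conclusion.** The concern holds as an internal inconsistency in an operative eligibility rule. The inequality contradicts its own label, and the connector leaves open whether the two conditions exclude jointly or separately. Taken literally, the rule excludes only patients with infarct ≤ 1/2 and mRS ≥ 3, and keeps every patient with infarct > 1/2. Correcting the sign alone would still leave two possible cohorts.

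Its size in patients is unknown. The article does not give the distribution of infarct size or baseline mRS among those screened, and it does not show which reading was used. A reader might infer a bias in the primary analysis or in the risk model, but the document does not demonstrate one.

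The conclusion assumes that the printed sign is what the authors published and that Table 1 is the rule used for screening. If the sign proved to be a conversion error, the ambiguity of the connector would remain. This is a correction to make, at modest severity.

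**What to change.** Amend exclusion criterion 3 in Table 1 so that:

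1. the inequality and the word 'large' agree, and the line says what the fraction refers to;
2. it is explicit whether the infarct and mRS conditions exclude only together or each on its own, with two numbered criteria if separately.

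The sponsor must settle the threshold and the clinical intent; this review proposes neither.

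Enrolment is planned from December 2021 to November 2024, so screening decisions may already have been taken. The sponsor should record which reading was actually applied, check the screening logs against the reconciled wording, and report how many classifications change, including if the answer is none.

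The cost is a one-line amendment and a log check. The sample size and the analysis methods need no change on this account.
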